#### Demographic characteristics questionnaire

Participants will complete the socio-demographic characteristics form including age, education level, income, occupation, ethnicity, gender and geographic area (province and city).

#### Cardiff fertility knowledge scale (CFKS)

The Persian version of the Cardiff Fertility Knowledge Scale (CFKS) will be used to assess the fertility knowledge. The CFKS consists of 13 items measuring knowledge about facts, risks and myths of fertility. Participants will respond to all items as true, false or do not know. A correct answer is assigned one point and an incorrect or ‘do not know’ answer is assigned zero point. Scores are reported as the percent correct score (0–100%). The Cronbach’s alpha coefficient of the CFKS was 0.79 and satisfactory for most countries [13].

#### Childbearing intention questionnaire

Parts of a questionnaire developed by Lampic et al. (2006) will be used in this study as the basis for the data collection regarding childbearing intentions that has satisfactory face validity and reliability and has previously been used by Lampic et al. (2006), Peterson et al. (2012) and Chan et al. (2014) in their studies of Swedish, American and Hong Kong university students [6, 16, 19]. The questionnaire contains five parts: (i) perceived knowledge of fertility issues (two items) asking about the perceived level of fertility-related knowledge; (ii) intention and potential obstacles of childbearing (seven items) including yes–no questions and open-response questions that aim to understand the ones’ intention to have children, as well as perceived obstacles; (iii) awareness of fertility issues (eight items) consisting of open-response items concerning changes in female fertility with age, and likelihood of pregnancy and infertility; (iv) importance of childbearing and intended behavior in the case of infertility (four items) containing four 0- to 10-point response scales assessing the perceived importance of childbearing and the preferred course of action in the case of infertility, and (v) conditions for parenthood (13 items) such as emotional readiness and financial stability that may be important in people’s decision to have children [16].

### Validity and reliability

After requesting the permission of the original authors, the instrument will be translated by a bilingual researcher into Persian, and the back-translation will be done independently by another bilingual researcher (in the field of reproductive health) and a native English speaker. An expert panel will be held and the questionnaire will be restructured based on their remarks and comments. Some of the questions may be revised based on cultural issues and the inclusion criteria in the current study. To determine the validity of the instrument, it will be provided to several experts in the field of reproductive health and their views will be collected and the instrument will be amended accordingly. Test-retest and Cronbach’s alpha coefficient will be used to estimate the reliability of the instrument.

### Sample size

According to our primary outcomes including fertility knowledge and intention toward childbearing that are important to be measured 3 months after the intervention, we considered a small standardized Cohen effect size (d = 0.2) with a type I error of 5% (α = 0.05) and a type II error of 10% (β = 0.1; power = 90%) and sample size obtained 527 in each group and considering 15% of loss to follow up, the sample size was calculated 620 couples in each group using the G-Power software. Considering the design effect equals to 1.5, final size was calculated 1240 couples in total (620 couples in each group). In each city around 200 couples (100 in each group) and from Tehran about 440 couples (220 in each group) will be recruited.

It should be noted that in order to compare quantitative outcomes between groups over time (baseline, 3, 12 and 18 month), the sample size obtained 660 couples in total (330 in each group) based on repeated measures ANOVA. So, the initial obtained sample size (620 couples in each group) will have the appropriate power for this analysis.

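### The design effect of 1.5 is stated but never applied: 620 couples per group allows for loss to follow-up only, and if the 1.5 holds, power is about 75%, not 90%

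*Protocol article*

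**What the plan says.** All of this is in the Sample size section of the protocol article. The calculation is for fertility knowledge and childbearing intention at 3 months.

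- Effect size: "we considered a small standardized Cohen effect size (d = 0.2".
- Error rates: "type I error of 5% (α = 0.05" and "type II error of 10% (β = 0.1; power = 90".
- Size before any inflation: "sample size obtained 527 in each group".
- Allowance for loss: "considering 15% of loss to follow up, the sample size was calculated 620 couples in each group using the G-Power software".
- Design effect: "Considering the design effect equals to 1.5, final size was calculated 1240 couples in total (620 couples in each group".
- Recruitment by city: "In each city around 200 couples (100 in each group) and from Tehran about 440 couples (220 in each group) will be recruited".

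The second paragraph of the section gives 330 couples per group for a repeated measures ANOVA. There it calls 620 per group the size obtained initially, although the sentence on the design effect calls the same number final.

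The Randomization section says that couples are assigned individually within each city in blocks of four, and that randomising by centre is not possible. It plans 110 blocks for Tehran and 50 for each of the other cities.

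**The concern.** A multiplier of 1.5 cannot leave a number unchanged. Either the factor was left out by mistake, or it does not belong in the calculation, or it refers to something the text does not name. These cases imply different power, so a reader cannot tell what power the trial has for the comparison that sets its size.

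This is more than a slip in one sentence. The 1240 carries through to the city quotas and the randomisation lists. Nor is it a detail that a short article leaves to a fuller document: the article sets out a derivation, and the derivation contradicts itself. The final report would probably repeat the 90% together with the 1.5.

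**Working it through.** **Inputs, all from the Sample size section:** d = 0.2; α = 0.05; power 90%; equal groups; 15% loss; design effect 1.5. The section does not say whether the test is one- or two-sided. I take it as two-sided, because that reproduces 527 whereas a one-sided test gives 429.

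**1. Reproduce 527.** The normal approximation is n = 2(1.960 + 1.2816)²/0.2² = 525.4, rounded up to 526. The t-test solution is 526.3, rounded up to 527. The stated figure is reproduced with no design effect; power at 527 per group is 90.0%.

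**2. Reproduce 620.** 527/(1 − 0.15) = 620.0. The loss allowance is the whole step from 527 to 620.

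**3. Apply the stated factor.** 527 × 1.5 = 790.5 evaluable couples per group, and 790.5/0.85 = 930 per group, or 1860 in total (931 and 1862 if 790.5 is first rounded up to 791). The plan recruits 4 × 200 + 440 = 1240. The block counts agree: (110 + 4 × 50) × 4 = 1240.

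**4. Could another route reach 620 with the 1.5 included?** Each row applies the factor and the 15% loss.

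| Variant | Couples per group |
|---|---|
| Two-sided, 90% power | 928 to 931 |
| One-sided, 90% power | 757 |
| Two-sided, 80% power | 694 |
| One-sided, 85% power | 635 |
| One-sided, 80% power | 547 |
| Repeated measures: 330 × 1.5/0.85 | 582 |
| Persons, two per couple: 527 × 1.5/(2 × 0.85) | 465 |

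None gives 620. The nearest, 635, needs a one-sided test and 85% power, which contradicts the stated 90% and does not start from 527.

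**5. Power at 620 recruited, 527 evaluable per group, d = 0.2.**

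| Meaning of the 1.5 | Effective n per group | Power |
|---|---|---|
| Not applicable; couple is the unit | 527 | 90.0% |
| Applies between couples | 527/1.5 = 351.3 | 75.4% (t), 75.5% (normal) |
| Partner correlation, both partners analysed | 2 × 527/1.5 = 703 persons | 96.3% |

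Normal approximation for the second row: 0.2 × √(351.3/2) = 2.651; 2.651 − 1.960 = 0.691; Φ(0.691) = 0.755. The effect detectable with 90% power is 3.2416 × √(2/351.3) = 0.245. Even with no loss at all, 620/1.5 = 413.3 and power is 82%.

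The third row reads the 1.5 as 1 + ICC for pairs, that is, an ICC of 0.5. This is my assumption; the article gives no ICC.

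**The case against.** The arithmetic is not in dispute. The case against concerns how much it matters.

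- *The 75% rests on the reading that fits the design least well.* Couples are randomised individually within city and allocation by centre is ruled out. Differences between cities or centres therefore do not inflate the variance of the treatment comparison as they would in a cluster trial. With the couple as unit, power is the stated 90%; on the partner reading it is higher. **This stands**, and it is why the 75% is conditional and why I do not ask for more couples.
- *The analysis named for outcomes over time is repeated measures ANOVA, and 620 covers it.* The article gives 330 per group for that analysis, and 330 × 1.5/0.85 = 582 is below 620. **This stands only in part.** The inputs behind 330 are not given, and it is an assumption that 330 precedes any allowance for loss. In any case it does not repair the 90% claimed for the 3-month comparison, which is what fixes the sample size.
- *The 527 carries no unit, and questionnaires are scored for each participant, so persons may be meant.* **This is possible**, but that route leads to 465 couples, not 620, and the text counts couples from the 620 onwards. The reading would show a surplus of power, yet it leaves the sentence unexplained.
- *The correction is one paragraph and changes neither allocation nor analysis.* **True**, but that speaks for the ease of the fix. A justification that contradicts itself should not remain in the record.

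**Conclusion.** The concern holds. The 620 per group includes 15% loss and no design effect, so the sentence that names a design effect of 1.5 is wrong as written. Taken at its word, the factor requires about 930 couples per group, 310 more than planned. With the planned numbers, it would put power for d = 0.2 at about 75% and the effect detectable with 90% power at d = 0.245.

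This does not show that the trial is underpowered. Depending on what the 1.5 means, power at 3 months is about 75%, 90% or 96%, and the article does not allow a choice between them. The design as described favours 90%, with the factor superfluous. All three figures assume a two-sided t-test and exactly 15% loss; the 96% also assumes that 1.5 equals 1 + ICC for two partners.

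**What to change.** Correct the paragraph; do not enrol more couples. The sponsor should say what the 1.5 was meant to represent and adopt the matching wording.

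1. **No design effect** (the reading that fits individual randomisation of couples). Delete the sentence and state: 620 couples per group, 527 evaluable after 15% loss, 90% power for d = 0.2 at two-sided α = 0.05 with the couple as unit; no design effect applied. The article does not name the unit of analysis, so the sponsor must confirm that it is the couple.
2. **The 1.5 applies between couples.** Keep it, give its source, and restate power as about 75% for d = 0.2, or 90% for d = 0.245.
3. **The 1.5 is correlation between partners.** Say so, give the ICC, and present the calculation in persons.

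In each case, reconcile the second paragraph of the section, where 620 is called the initial size, with the sentence that calls it final.

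The cost is one rewritten paragraph and, under option 2, a less favourable power statement. City quotas and randomisation lists stay as they are. Applying the factor in full would take 1860 − 1240 = 620 more couples, which nothing in the described design calls for.

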### Randomization

Samples will be selected through stratified sampling and random samples are then selected from each stratum. The strata consist of five cities, and separate randomization lists will be prepared for each city using a block randomization.

Due to the limited number of main public centers providing compulsory premarital counselling in each city (3 centers in Tehran, 2 centers in in Ahvaz, 1 center in Shiraz, 2 centers in Tabriz and 3 centers in Mashhad), and other concerns such as selection bias, and generalizability (according to potential confounder of socioeconomic status), the cluster randomization based on the centers is not possible. So, we will use central randomization that is stratified to the cities.

The PI will randomly assign the couples into two groups in each city by a computer-generated random sequence. For randomization, the permuted block randomization will be used (block size = 4). According to the sample size of 440 identified, 110 blocks will be produced using the online site (www.sealedenvelope. com) for Tehran. According to the sample size of 200 identified, 50 blocks will be produced using the online site (www.sealedenvelope. com) for other cities.

Allocation will be concealed by using sequentially numbered opaque sealed envelopes that contain group assignments determined by computer-generated random sequences.

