### Statistical method

Categorical variables will be presented by frequency (%), and quantitative variables will be reported as means (SD) or medians (with 25th to 75th quartiles), as appropriate. Graphical approach, numerical indices and the Shapiro-Wilk test will be used to evaluate the normality distribution and Leven test for homogeneity of variances in quantitative variables, respectively.

Comparisons between groups at baseline will be performed using Chi-square or Fisher-exact test for categorical variables, Independent samples t-test for normally distributed quantitative variables and Mann–Whitney U test for non-normally distributed quantitative variables. To compare the outcomes between the two groups over the time, repeated measures ANOVA will be used. Data will be analyzed using the SPSS software version 22 (IBM Corp. IBM SPSS Statistics for Windows, Armonk, NY, USA). For all analyses, a *P* value < 0·05 will be considered statistically significant.

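### The 660-couple repeated measures ANOVA figure fits only a group effect averaged over four waves including baseline, and neither test that this ANOVA offers is the 3-month contrast on which the trial is sized

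*Protocol article*

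**What the plan says.** The Sample size section of the protocol article sizes the trial on fertility knowledge and childbearing intention, outcomes "that are important to be measured 3 months after the intervention, we considered a small standardized Cohen effect size (d = 0.2"). It sets a "type I error of 5% (α = 0.05") and a "type II error of 10% (β = 0.1; power = 90"%), and reports that the "sample size obtained 527 in each group". Allowing 15% loss, this becomes 620 couples per group, 1240 in total.

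A second paragraph in that section turns to quantitative outcomes compared over baseline, 3, 12 and 18 months. It reports that "the sample size obtained 660 couples in total (330 in each group) based on repeated measures ANOVA", and concludes that 620 couples per group is therefore adequate for this analysis. It gives no tested effect, effect size, correlation, power or loss allowance for the 660.

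The Statistical method section states: "To compare the outcomes between the two groups over the time, repeated measures ANOVA will be used". It does not say whether the group effect or the group-by-time interaction decides the comparison. Under Randomization, "separate randomization lists will be prepared for each city using a block randomization", so city is the stratum.

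**The concern.** A repeated measures ANOVA with baseline as an outcome wave offers two tests that involve the arms: a group effect averaged over all waves, and a group-by-time interaction. The average includes a wave at which randomisation makes the expected difference zero, so it understates any follow-up effect. The interaction asks whether the difference varies anywhere across the four waves. Neither estimates the arm difference at 3 months, the time point the sample size text singles out.

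If 660 was computed as though d = 0.2 were present at all four waves, it is too small for a follow-up effect of that size, and the reassurance drawn from it is weaker than it looks. The baseline score is also used as a diluting outcome when it could serve as a covariate that sharpens the 3-month comparison.

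**Working it through.** **Inputs.** From the Sample size section: d = 0.2, alpha 0.05, power 90%, four waves, 15% loss. Taken as two-sided, because 527 per group reproduces only that way. Not in the document: the correlation between waves, ρ. I assume 0.5 and show 0.3 and 0.7. All waves are taken to have equal variance and equal correlation.

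**Main calculation.** A two-sided t-test at d = 0.2 with 90% power needs 527 per group, and 527 / 0.85 = 620. Both stated figures reproduce.

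**The 660.** For the between-group test in a repeated measures ANOVA with total N, m waves and f = d/2:

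λ = f² · N · m / (1 + (m − 1)ρ), referred to F with 1 and N − 2 degrees of freedom.

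With f = 0.1, m = 4, ρ = 0.5 and N = 660: λ = 0.01 × 660 × 4 / 2.5 = 10.56, power 0.9006. At N = 658 power is 0.8997. So 660 is the smallest even total that reaches 90%, with no allowance for loss.

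The alternatives tried do not match the stated d, power and four waves together:

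- Interaction with f = 0.1, m = 4, ρ = 0.5: 180.
- Between-group test with three waves, ρ = 0.5: 704.
- Settings that come within 3% of 660 need 80% power, or three waves with a smaller effect size.

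**Baseline set to zero.** With differences of 0, 0.2, 0.2 and 0.2, the four-wave mean is 0.6 / 4 = 0.15, so f = 0.075. At N = 660 and ρ = 0.5: λ = 0.005625 × 660 × 4 / 2.5 = 5.94, power 68%. Reaching 90% for this test needs 1170 complete couples at ρ = 0.5 (890 at 0.3, 1450 at 0.7).

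For the interaction, λ = (N/4) · Σ(δ − mean δ)² / (1 − ρ), with 3 and 3(N − 2) degrees of freedom. Here the sum of squares is 0.15² + 3 × 0.05² = 0.03.

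| Total complete couples | Test | ρ = 0.3 | ρ = 0.5 | ρ = 0.7 |
|---|---|---|---|---|
| 660 | group effect | 80% | 68% | 59% |
| 660 | interaction | 59% | 76% | 94% |
| 1054 (527 per arm) | group effect | 94% | 87% | 79% |
| 1054 | interaction | 81% | 93% | 99.5% |
| 1240 (no loss) | group effect | 97% | 92% | 85% |
| 1240 | interaction | 88% | 96% | 99.9% |

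The two tests respond to ρ in opposite directions, so leaving both the test and ρ unstated leaves the power open.

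**The 3-month contrast adjusted for baseline.** Power ≈ Φ(0.2 · √(527/2) / √(1 − ρ²) − 1.96). Here 0.2 × √263.5 = 3.247.

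- Unadjusted: Φ(3.247 − 1.96) = Φ(1.287) = 90%.
- ρ = 0.3: Φ(3.247 / 0.954 − 1.96) = Φ(1.443) = 93%.
- ρ = 0.5: Φ(3.247 / 0.866 − 1.96) = Φ(1.789) = 96%.

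**The case against.** The strongest reply is that the trial is not run at 660. The protocol attaches its power claim to 620 per group, the 660 is a secondary check, and because it is smaller than 1240 it changed nothing in the design. The 3-month comparison has its own calculation. This stands. A reader might infer from the 68% that the trial is underpowered, and the documents do not support that: at ρ = 0.5 the recruited sample gives 87% to 96%, depending on the test and the loss.

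Second, the protocol does not name the tested effect. Matching 660 suggests how the number was produced, not which effect will be reported, and the phrase about comparing groups over time fits an interaction at least as well. This also stands, so the group effect and ρ = 0.5 are inferences. It does not rescue the 660, since at ρ = 0.5 the interaction has only 76% there.

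Third, harsher scenarios are tempting. With an effect fading from 0.2 to 0.1 to 0.05, the group effect has 43% power at 1054 and ρ = 0.5. No such fading appears in the documents, and the interaction would still have 82% under it. Nor do they state a 15% loss at every wave; they give 15% once.

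Fourth, a reader might infer that couples with a missed wave will be dropped and that city will be ignored. Dropping incomplete cases is the usual behaviour of classical repeated measures ANOVA, but the article does not say it will happen. Missing-data handling and covariates may sit in an analysis plan that is not shown. I do not count either as an error, and leaving out city plays no part in the shortfall at 660.

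**Conclusion.** The point holds for the supporting calculation and the choice of test. On the inferred inputs, 660 rests on a difference of 0.2 at baseline as well as at follow-up. With the expected baseline difference at zero and d = 0.2 at all three follow-ups, it gives about 68% power for the group effect (59% to 80% over ρ from 0.7 to 0.3).

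The conclusion that 620 per group is adequate roughly survives at ρ = 0.5 but is not secure across plausible correlations: after 15% loss, 79% for the group effect at ρ = 0.7 and 81% for the interaction at ρ = 0.3. Neither test is the 3-month contrast on which the trial is sized.

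All of this assumes a sustained effect, equal correlation between waves and one score per couple. The design effect of 1.5 mentioned in the same section is a separate matter and is not built into these figures.

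**What to change.** For quantitative outcomes, replace the repeated measures ANOVA that treats baseline as a wave with a linear mixed model on the 3, 12 and 18-month scores:

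- Fixed effects: arm, time, arm by time, baseline score, and city as the randomisation stratum.
- Correlation between a participant's repeated scores allowed for, and a random effect or clustering term for couple if both partners' scores are analysed.
- All available follow-up data included.
- The arm difference at 3 months named as the primary contrast, with 12 and 18 months secondary.

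Delete the 660 statement, or restate it for the 3-month contrast with its correlation and loss allowance.

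The cost is wording in the protocol or analysis plan and a little more analysis work. The planned SPSS package can fit mixed models. Baseline score and city are already collected, and recruitment does not change.

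### The 660-couple figure for the repeated measures ANOVA credits the pre-intervention baseline with the full effect; without that, 330 per group has about 68% power rather than 90%, so the stated margin is overstated although 620 per group can stand

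*Protocol article*

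**What the plan says.** The Sample size section of the protocol article contains two calculations.

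The first sets recruitment. For knowledge and intention at 3 months the authors write "we considered a small standardized Cohen effect size (d = 0.2"). Alpha is 0.05 and the target power is 90%. The result is 527 per group, which an allowance for attrition then raises: "considering 15% of loss to follow up, the sample size was calculated 620 couples in each group".

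The second is offered as reassurance about the longitudinal analysis. It applies "in order to compare quantitative outcomes between groups over time (baseline, 3, 12 and 18 month"), and states that "the sample size obtained 660 couples in total (330 in each group) based on repeated measures ANOVA". The paragraph ends: "So, the initial obtained sample size (620 couples in each group) will have the appropriate power for this analysis".

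The second calculation gives no effect size, correlation, loss to follow-up or tested term of its own. The Statistical method section names repeated measures ANOVA for comparing the groups over time and does not say whether the group main effect or the group-by-time term is the test of interest. Table 1 places the first outcome assessment at allocation, before the 3-, 12- and 18-month follow-ups.

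**The concern.** A repeated measures calculation for a group main effect concerns the difference between arms averaged over every visit entered. If baseline is one of those visits, the average includes a time at which the training has not happened and at which randomised arms are expected to be equal. A formula that assumes one common d at all visits then counts an effect that cannot be there.

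The protocol uses the resulting number to tell the reader that the longitudinal analysis needs only about half the trial (660 of 1240 couples). If the number is wrong, that margin is wrong too. The same choice would carry into the analysis: a main effect averaged over four visits, one of them necessarily null, reports three quarters of the follow-up effect.

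**Working it through.** **Inputs from the Sample size section:** d = 0.2, so f = d/2 = 0.1 for two equal groups; alpha 0.05; power 90%; m = 4 visits including baseline; 15% loss; 620 couples recruited per group. **Assumed:** correlation r between visits, which is not stated, and compound symmetry. I use r = 0.5 because it reproduces the protocol's figure, and show other values. N is the total number of couples and n the number per group.

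**1. The recruitment figure.** The exact two-sided t-test at d = 0.2 gives 89.98% power at n = 526 and 90.04% at n = 527. 527/0.85 = 620. Both protocol figures reproduce.

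**2. The 660.** Between-groups test: λ = f²·N·m / (1 + (m − 1)r), on 1 and N − 2 degrees of freedom.
- N = 660: λ = 0.01 × 660 × 4 / 2.5 = 10.56, power 90.06%.
- N = 658: power 89.97%.

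So 660 is the exact answer at r = 0.5. Neighbouring settings do not fit: the same formula gives 580 at r = 0.4 and 738 at r = 0.6; three visits at r = 0.5 give 704; group-by-time at r = 0.5 gives 180 at f = 0.1 or 710 at f = 0.05.

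**3. Same formula, no baseline effect.** Differences of 0, 0.2, 0.2, 0.2 average (0 + 0.2 + 0.2 + 0.2)/4 = 0.15. Then λ = (N/4) × 0.15² × 4 / (1 + 3r) = 0.0225·N / (1 + 3r).

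| N (per group) | r | λ | Power, group main effect |
|---|---|---|---|
| 660 (330) | 0.5 | 5.94 | 68.2% |
| 1054 (527) | 0.3 | 12.48 | 94.2% |
| 1054 (527) | 0.4 | 10.78 | 90.7% |
| 1054 (527) | 0.5 | 9.49 | 86.8% |
| 1054 (527) | 0.7 | 7.65 | 78.9% |
| 1170 (585) | 0.5 | 10.53 | 90.0% |
| 1240 (620, no loss) | 0.5 | 11.16 | 91.6% |

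At r = 0.5, 90% power therefore needs 585 evaluable per group. With 15% loss, 585/0.85 = 688.2, or 689 per group.

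**4. Group-by-time, same pattern.** Deviations from the mean are −0.15, 0.05, 0.05, 0.05, with sum of squares 0.0225 + 3 × 0.0025 = 0.03. λ = (N/4) × 0.03 / (1 − r), which is 0.015·N at r = 0.5, on 3 and 3(N − 2) degrees of freedom.
- N = 660: λ = 9.90, power 75.5%.
- N = 1054: λ = 15.81, power 93.1%.
- 90% needs N = 948.

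This test moves the other way with r: at N = 1054 it has 81.5% at r = 0.3 and 99.5% at r = 0.7.

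**5. Follow-up visits only.** Mean of months 3, 12 and 18, difference 0.2: λ = (N/4) × 0.2² × 3 / (1 + 2r) = 0.015·N at r = 0.5, on 1 and N − 2 degrees of freedom.
- 90% needs N = 704, or 352 evaluable per group; 352/0.85 = 414.1, so 415 recruited per group (830 couples).
- N = 1054: 97.8% (99.3% at r = 0.3, 95.2% at r = 0.7).

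**The case against.** The strongest reply is that the operative conclusion survives. The 660 does not set recruitment; the 3-month comparison does, and that calculation reproduces. At r = 0.5 and after 15% loss, the trial has 87% power for the main effect, 93% for group-by-time and 98% for the follow-up average. In a pre-test/post-test design group-by-time is a natural reading of the analysis, and which term is tested may be settled in an analysis plan that is not shown. All of this stands, and it limits the point to the figure and the margin it implies.

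A reader might infer more: that 90% power needs more couples than the trial recruits. The documents do not support that as a general statement. The need is 1170 couples with data, fewer than the 1240 recruited. It exceeds recruitment only after 15% loss is added (2 × 689 = 1378), only if the group main effect is the test, and only at a correlation of about 0.5 or more; at r = 0.4 the 527 completers already give 90.7%.

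The correlation is indeed inferred. With no baseline effect, 660 couples would have about 90% power if r were near 0.14. Nothing in the protocol points to that value, whereas one common d with r = 0.5 returns 660 exactly.

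The missing loss allowance on the 660 has no consequence of its own: 330/0.85 = 388.2, or 389 per group, well under 620. Nor can a shortfall be built on an effect that fades by months 12 and 18, because the protocol gives no effect sizes for those visits.

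**Conclusion.** The concern holds for the figure and not for the size of the trial. The stated 660 couples rest on a calculation that gives a pre-intervention visit the full 0.2 SD effect. On the protocol's own d, with zero difference at baseline and r = 0.5, 330 per group has 68% power for the group main effect and 76% for group-by-time, so neither test of the four-visit ANOVA reaches 90%. For the main effect the requirement is 585 evaluable per group, which is 77% more than stated (585/330 = 1.77).

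The claim that 620 per group is adequate largely survives: 86.8% to 97.8% at r = 0.5 after loss, depending on the contrast. What does not survive is the implication that about half the trial would do. These results assume compound symmetry, an effect of 0.2 SD at all three follow-ups, and the inferred r; the identification of the formula rests on the exact match at 660.

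**What to change.** In Sample size, delete the 660-couple figure and replace it with a calculation for the group difference averaged over months 3, 12 and 18. At d = 0.2, r = 0.5 and 90% power this is 352 evaluable couples per group, or 415 per group after 15% loss, and the 527 expected completers give about 98%. State the correlation and the loss used. In Statistical method, make that post-baseline contrast the between-group comparison.

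If baseline is kept as a fourth outcome level and the group main effect is tested, restate the figure as 585 evaluable per group and the power at 527 as about 87% (94% at r = 0.3, 79% at r = 0.7).

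The cost is a few sentences in two sections and no additional couples. The only downside is that, under the second option, the stated power falls slightly below the 90% target.
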